### Outcomes {12}

The primary outcome of this study will be the END within 7 days. END will be defined as a 2-point increase in the NIHSS score or a 1-point increase in motor function (specifically NIHSS Items 5, 6, and 7) within 24 h to 7 days of AIS onset. To address the potential impact of END severity on the reliability of the primary outcome, we will conduct a sensitivity analysis using a higher threshold: a 4-point worsening in the NIHSS or a 2-point increase in motor function, which will be classified as severe END.

The secondary outcomes of the study will include:Evaluation the rate of good prognosis at 30 and 90 days. Good prognosis will be defined as a modified Rankin Scale (mRS) score of 2 or lower, which indicates either no disability or minor disabilityAssessment of the recurrence rate of symptomatic cardiovascular and cerebrovascular events within 90 daysAnalysis of changes in blood biochemical indices (including liver function, renal function, lipid profile, etc.) before and after treatment, measured at baseline, 7 days, 30 days, and 90 daysExamination of changes in inflammatory factors (interleukin-6, IL-6; interleukin-8, IL-8; tumor necrosis factor-alpha, TNF-α) before and after treatment, assessed at baseline and 7 days

Safety outcomes will be documented by recording the types and frequencies of all adverse events and abnormalities in laboratory tests throughout the study duration. Safety evaluations will include assessments of the patients’ general condition, vital signs, blood routine tests, blood biochemistry, liver and kidney function, coagulation function, and neuroimaging examinations. All participants will undergo assessments before treatment initiation and at the initial treatment milestones of 30 days and 90 days.

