### Sample size {14}

This study is a randomized controlled trial with the intervention group as the PI group and the control group as the AT group. The study involves AIS patients with a confirmed history of CHD, and the primary outcome is the END in the two groups.

Based on our retrospective observation of 21 AIS patients with a history of CHD and no prior use of PCSK9 inhibitors, hospitalized at the First Affiliated Hospital of Dalian Medical University from April 2022 to June 2023, a total of 7 patients exhibited END within 24 h to 7 days of disease onset, accounting for 33.3%. During the same period, among 22 AIS patients with a history of CHD who were treated with PCSK9 inhibitors within 24 h of onset, 3 patients experienced END, accounting for 13.6%. Assuming the incidence of END in the intervention and control groups are 13.6% and 33.3%, respectively, with a two-sided α level of 0.05 and 80% power, we used the PASS software version 15 (NCSS, LCC, Taiwan 2017) to calculate the sample size. Each group requires 70 patients. Considering a 10% loss to follow-up, both groups will need 78 patients, making a total of at least 156 patients across both groups. The sample size calculation formula is as follows:$$n=2({Z}_{\alpha /2}+{Z}_{\beta }{)}^{2}\cdot p(1-p)\div (\delta {)}^{2}$$where:

*n* is the sample size per group.

*Z*_α_/2 is the critical value for a two-sided significance level (1.96 for *α* = 0.05).

Z_*β*_ is the critical value for power (0.84 for 80% power).

*p* is the estimated overall incidence rate.

*δ* is the expected difference between the two groups.

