## Statistical methods

### Statistical methods for primary and secondary outcomes {20a}

Once all participants have completed their assessments, data analysis will commence. To reduce bias, the data analyst will remain blinded during the analysis process. Only participants who strictly adhere to the intervention protocol will be included in the analysis. Data that are missing or deviate from the protocol will be excluded from the analysis.

The primary and secondary outcomes will be combined as dependent variables in the generalized linear model (GLM). First, a univariate analysis of the treatment groups will be performed to determine the unadjusted risk ratio (RR) and odds ratio (OR), along with a 95% confidence interval (CI). Next, continuous variables like the NIHSS score at admission, mRS score, and age will serve as covariates. Categorical variables such as sex, hypertension, diabetes, and prior strokes will be included as factors in the GLM to reduce variance error. If the outcomes show statistical significance for the main effects, interaction effects will be used to assess differences between the groups. Changes in blood biochemical indices will be analyzed using repeated measures ANOVA or mixed-effects models, accounting for measurements taken at baseline, 7 days, 30 days, and 90 days. Changes in inflammatory factors (IL-6, IL-8, TNF-α) from baseline to 7 days will be evaluated using paired *t*-tests or Wilcoxon signed-rank tests, based on data distribution. Sensitivity analysis will use the criterion for severe END, defined as either a 4-point increase in NIHSS or a 2-point worsening in motor function based on a higher threshold. All analyses will be conducted using SPSS (IBM Corp., Armonk, NY, USA), with a significance threshold of *α* = 0.05.

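### Section {20a} assigns the comparison between arms to interaction effects after significant main effects; for END that difference is the treatment main effect, and no comparison is named as primary

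*Protocol article*

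**What the plan says.** Outcomes {12} sets a single binary primary outcome: "The primary outcome of this study will be the END within 7 days".

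Statistical methods {20a} then describes the analysis in four steps:

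- On the response: "The primary and secondary outcomes will be combined as dependent variables in the generalized linear model (GLM").
- On the first comparison: "a univariate analysis of the treatment groups will be performed to determine the unadjusted risk ratio (RR) and odds ratio (OR"), with 95% confidence intervals.
- On adjustment: admission NIHSS, mRS and age enter as covariates, and sex, hypertension, diabetes and prior stroke as factors. Both lists are worded as examples, not as closed lists.
- On judging the arms: "If the outcomes show statistical significance for the main effects, interaction effects will be used to assess differences between the groups".

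The section does not say which main effects open the last step, which interaction is then tested, or whether the unadjusted or the adjusted result is primary. It gives the biochemical indices and the inflammatory markers their own methods.

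Sample size {14} rests on a direct comparison of two proportions: "Assuming the incidence of END in the intervention and control groups are 13.6% and 33.3%, respectively". The test there is two-sided at 0.05, and the target power is 80%. Additional analyses {20b} places interaction tests, by logistic regression, with the subgroup work.

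**The concern.** With two arms and one binary outcome, the treatment coefficient carries the difference between arms. A treatment-by-sex or treatment-by-diabetes coefficient answers another question: whether the effect differs between subgroups. If evolocumab lowers the odds of END equally in everyone, every such interaction is zero on the odds-ratio scale, however large the benefit. The stated rule therefore uses the wrong parameter for judging the arms, and uses it only after an earlier test has succeeded.

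Two weaknesses in the same section add to this. Because neither the unadjusted nor the adjusted comparison is designated primary, the choice could be made after both are seen. And the sentence on combining outcomes leaves unclear whether END has a model of its own. At stake is whether the reported test is the one the trial was sized for.

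**Working it through.** **1. What the trial was sized for.** Inputs from {14}: 13.6% and 33.3%, two-sided 0.05, 80% power. The mean rate is p = (0.136 + 0.333)/2 = 0.2345 and δ = 0.333 − 0.136 = 0.197.

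- Printed formula: 2 × (1.96 + 0.84)² × 0.2345 × 0.7655 / 0.197² = 72.5 per group.
- Unpooled variance: (1.96 + 0.8416)² × (0.136 × 0.864 + 0.333 × 0.667) / 0.197² = 68.7.
- Arcsine: 69.6, which rounds up to 70.
- Pooled-variance formula: 72.

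The plan says "Each group requires 70 patients", so the figure is reproduced to within a few patients. Then 70/0.9 = 77.8, which gives the stated 78. Power for the direct comparison is 79.2% at 70 per group and 83.4% at 78. The design therefore rests on a main-effect test of END.

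**2. The three places side by side.** {14} compares the two END proportions directly. The opening of {20a} compares the arms by risk ratio and odds ratio. {20b} treats interactions as additional. Only the later sentence in {20a} assigns the group difference to interactions.

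**3. The literal rule under a homogeneous effect.** The documents name no interaction, so this is an illustration. Assumptions: an evenly split binary factor; 70 per arm, so 35 per cell; a common odds ratio of (0.136/0.864)/(0.333/0.667) = 0.32; a pooled z-test for treatment; a Wald test for the interaction on the log-odds scale; 200,000 simulated trials.

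| Test | Planned effect true | No effect (33.3% in both arms) |
|---|---|---|
| Treatment main effect | 80.3% | 5.0% |
| Interaction alone | 3.6% | 4.6% |
| Both, as the rule requires | 2.8% | 0.2% |

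If the factor also predicts END (a log-odds difference of 1.0), both tests reject in 2.5% of trials under the planned effect. If a significant main effect of either treatment or the factor opens the step, the figures are 2.8% without and 3.0% with that prognostic effect.

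**4. A scenario kinder to the rule.** Suppose the interaction is as large as the main effect and the factor is evenly split. Its standard error is about twice that of the main effect, so a test with 80% power for the main effect (1.96 + 0.84 = 2.80) has an expected z of 2.80/2 = 1.40 for the interaction. Power is Φ(1.40 − 1.96) = Φ(−0.56) = 0.288, about 29%. The two-step rule cannot exceed that.

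**The case against.** **A valid comparison is already there.** A reader might infer that the protocol defines no valid test of treatment on END. The documents do not support this. The unadjusted risk ratio and odds ratio with 95% CI are a valid comparison of the arms, END is the stated primary outcome, and the 0.05 level is given. Main effects are also tested before any interaction. This stands and limits the point: the section contradicts a comparison it already contains.

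**Combining need not mean merging.** A reader might also infer that END, mRS, recurrence and laboratory values are merged into one response, so that no p-value belongs to END. But the laboratory outcomes have separate methods, and a risk ratio can only be formed for one binary outcome at a time. Modelling each outcome in turn is a natural reading. What remains is ambiguity.

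**Effect measure and link.** A condensed article may leave these to the analysis plan. At the planning rates the risk ratio is 0.136/0.333 = 0.41 and the odds ratio 0.32. Unadjusted, both come from the same table and share a null hypothesis, so giving both is not a fault in itself. The choice between unadjusted and adjusted is a real one.

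**Group-by-time terms.** In a repeated-measures model a group-by-time interaction does compare arms. That could explain the sentence for the biochemical indices. However, the sentence precedes those methods and follows the GLM for the primary and secondary outcomes, and END is one binary result per patient.

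**No inflated error.** The gate is written in advance and does not raise false positives. With no treatment effect it declares a difference in 0.2% of simulated trials, and in 3.5% at most if any main effect opens it and the factor is prognostic. That is correct; the cost is power and interpretation.

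**Conclusion.** The interaction sentence in {20a} is wrong as written for END. It assigns the difference between arms to a parameter that measures effect modification, against the rest of {20a}, against {14} and against {20b}. This holds whichever way the sentence on combining outcomes is read. In addition, that sentence is ambiguous, and neither the unadjusted nor the adjusted comparison is designated primary.

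Followed literally, the rule would declare a difference in about 3% of trials, against about 80% for the main-effect test. That figure rests on a homogeneous odds ratio and an evenly split factor, neither of which the documents give. With an interaction as large as the main effect, the ceiling is about 29%. The figures show the cost of the literal rule; they do not forecast what the analyst will do, since the unadjusted comparison is also specified.

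**What to change.** Revise {20a} as follows:

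1. State that each outcome is analysed separately, in its own model.
2. Designate one comparison of END between arms as the primary analysis: the treatment main effect, with its estimate, 95% CI and two-sided 0.05 test, on one named effect measure. If it is adjusted, close the covariate list, draw it from the variables {20a} already names, and include sex, the randomisation stratum in {16a}. Label the other comparison (unadjusted or adjusted) supportive.
3. Delete the interaction sentence, or move it to {20b} as exploratory.

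The cost is wording only. The 70 per group, and 78 after allowance for loss, stay as they are because they already rest on the main-effect comparison. No data collection changes. Under {21b} analysis starts only once all participants have finished, so the change should be made and dated before then.

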### Follow-up

The follow-up period will start on day 8 after enrollment and continue until day 90, with evaluations on days 30 and 90. Assessments will include concomitant medications, adverse events, physical examinations, laboratory tests, NIHSS and mRS scores, and the occurrence of any recurrent cardiovascular or cerebrovascular events. If a participant experiences an endpoint event (recurrent cardiovascular or cerebrovascular event) during treatment or follow-up, the clinical study will be terminated, and active management will be initiated.

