### Methods in analysis to handle protocol non-adherence and any statistical methods to handle missing data {20c}

To address protocol non-adherence, we will define the analysis populations as follows: the intention-to-treat (ITT) population will include all randomized participants who have at least one treatment record and will be used for analyzing the primary outcome. The per-protocol (PP) population will include only those participants who fully adhere to the study protocol without major deviations and will be used for analyzing the secondary outcomes. Experience indicates that dropouts are rare. If the proportion of missing data exceeds 10%, multiple imputation techniques will be employed to ensure the robustness of our study results.

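### The repeated-measures ANOVA option for LDL-C and the other biochemical indices can drop partly observed participants and is less precise than a baseline-adjusted model; one mixed model should be named instead

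*Protocol article*

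**What the plan says.** Outcomes {12} makes changes in blood biochemical indices a secondary outcome, covering liver function, renal function and the lipid profile, with draws at baseline and days 7, 30 and 90. The analysis is given in one sentence of {20a}: "Changes in blood biochemical indices will be analyzed using repeated measures ANOVA or mixed-effects models, accounting for measurements taken at baseline" and at the three follow-up visits. No rule is given for choosing between the two methods.

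The covariates are named just before, for the generalized linear model: "continuous variables like the NIHSS score at admission, mRS score, and age will serve as covariates", with sex, hypertension, diabetes and prior stroke as factors. The baseline laboratory value is not on that list.

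Four other statements bear on the point:

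- {20a} on missing data: "Data that are missing or deviate from the protocol will be excluded from the analysis".
- {20c} on missing data: "If the proportion of missing data exceeds 10%, multiple imputation techniques will be employed". The unit in which the 10% is counted is not stated.
- {20c} on the per-protocol population: it "will be used for analyzing the secondary outcomes".
- Follow-up, on a participant with a recurrent cardiovascular or cerebrovascular event: "during treatment or follow-up, the clinical study will be terminated, and active management will be initiated".

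The Discussion states that the trial will confirm the LDL-C-lowering effect.

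**The concern.** Classical repeated-measures ANOVA needs a complete row of measurements. If baseline and the three follow-up draws are the four levels of time, a participant without a day-90 sample also loses the day-7 and day-30 values already in the database. The exclusion rule in {20a} points the same way. The Follow-up section makes such gaps plausible in a particular group: if participation ends at a recurrent event, later draws may be absent for the very patients who had events, so the completers may be a selected group.

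The second issue is precision. With baseline as a level of time and no adjustment for it, the treatment effect is read from the pre/post contrast between arms. That contrast has the variance of a change score, which is larger than that of a baseline-adjusted comparison unless baseline and follow-up are perfectly correlated.

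At stake is how well the trial estimates its LDL-C effect, and whether the method can be chosen after the data are seen. The END conclusion is not affected.

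**Working it through.** **Inputs from the document.** Four time points ({12}, {20a}); 156 randomised, 78 per arm, with 10% loss planned (Sample size {14}).

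**Inputs assumed.** The article gives no missingness by visit and no correlation between visits. I take baseline as complete, 3-8% missing independently at each follow-up visit, and equal variances with equal correlation r of 0.4-0.7 between any two visits.

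**The plan's own figure.** No power or sample size is stated for the biochemical outcomes. The only such figure concerns END: 70 per group, then 70/0.9 = 77.8, rounded up to 78, so 156 in total. It is used below only as the denominator.

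**Step 1: complete cases under ANOVA.** With missingness m per visit, the complete share is (1 - m)^3.

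| m | complete share | of 156 |
|---|---|---|
| 3% | 0.97^3 = 0.913 | 142 |
| 5% | 0.95^3 = 0.857 | 134 |
| 8% | 0.92^3 = 0.779 | 121 |

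If instead the planned 10% loss is pure dropout, 0.90 x 156 = 140 remain, about 90%.

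**Step 2: does imputation step in?** The answer depends on how the 10% in {20c} is counted. With baseline complete, the share of all four values that is missing is 3m/4.

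| m | participants incomplete | values missing |
|---|---|---|
| 3% | 8.7% | 2.25% |
| 5% | 14.3% | 3.75% |
| 8% | 22.1% | 6.0% |

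Counted in participants, imputation is triggered at 5% and 8% per visit but not at 3%. Counted in values, it is triggered in none of these cases. The exclusion rule in {20a} would also have to give way to it.

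**Step 3: precision.** Set the variance at each visit to 1. The mean of the three follow-up values has variance (1 + 2r)/3 and covariance r with baseline. The factor 2/n for an arm difference is common to both methods and cancels.

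- Change score (post-treatment mean minus baseline): (1 + 2r)/3 + 1 - 2r
- Baseline-adjusted: (1 + 2r)/3 - r^2

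The first minus the second is 1 - 2r + r^2 = (1 - r)^2, which is never negative, so under these assumptions adjustment cannot be the less precise choice.

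| r | change score | adjusted | ratio |
|---|---|---|---|
| 0.4 | 0.800 | 0.440 | 0.55 |
| 0.5 | 0.667 | 0.417 | 0.625 |
| 0.7 | 0.400 | 0.310 | 0.775 |

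The adjusted variance is thus about 55-78% of the change-score variance. At a single visit the ratio is (1 - r^2)/(2(1 - r)) = (1 + r)/2, which is 0.70 at r = 0.4 and 0.85 at r = 0.7.

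**The case against.** The strongest reply is that the same sentence permits mixed-effects models. A mixed model keeps participants with partial data. It also matches baseline adjustment in precision, either with baseline as a covariate or with baseline as a response and the arm means constrained equal there. A condensed article may leave the choice and the model details to an analysis plan. This stands: both defects belong to the ANOVA branch. It does not remove the point, because the article itself lists the weaker method as acceptable.

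A reader might infer four stronger things that the text does not support:

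- **That baseline is wasted.** It serves at least as the reference for change. The wording also does not expressly fix baseline as an outcome or rule it out as a covariate; the time-level reading is only the more natural one.
- **That anyone with a missing visit is always dropped.** {20c} offers multiple imputation above 10% missing, although its unit is unstated and it conflicts with {20a}.
- **That the LDL-C test is the arm main effect over four time points**, which would be 3/4 of a constant post-treatment effect. The rule of looking at interactions only after significant main effects follows the generalized linear model; the biochemical indices then get their own sentence. It is not clear that the rule carries over.
- **That estimates by visit are ruled out.** Nothing says so, and both methods can give them.

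It is also fair to say that part of any completer selection comes from the per-protocol population set for secondary outcomes. Removing the ANOVA option would not change that.

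**Conclusion.** The point holds for the ANOVA option only. If that option is used with baseline as a time level, and imputation is not triggered, about 9-22% of participants would be lost under the assumed 3-8% independent missingness per visit, or about 10% under pure dropout at the planned rate. The pre/post contrast would also forgo a variance reduction of about 22-45% at assumed equal correlations of 0.4-0.7. These sizes rest on the assumed missingness and correlations; the directions follow from the methods themselves. The outcomes are secondary and no power is claimed for them, so this is a minor, free improvement and not a threat to the trial's main conclusion.

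**What to change.** In {20a}, delete repeated-measures ANOVA and name one linear mixed model for the day-7, day-30 and day-90 values. It should contain arm, visit, arm-by-visit, the baseline value of the index, baseline-by-visit, and sex, which is the stratification factor in Sequence generation {16a}. It should use all available data, so that a missed visit does not remove the participant's other values. Report the arm difference with 95% CI at each visit, LDL-C first. A mixed model with baseline as a response and equal baseline means in the two arms is an acceptable equivalent.

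The missing-data statements in {20a} and {20c} should be reconciled in the same edit, so that the exclusion rule does not undo the gain.

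The cost is wording only. No new data are needed, and the software already named ("All analyses will be conducted using SPSS") can fit the model.

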### Interim analyses {21b}

Not applicable to the study. Data analysis will not commence until all participants have completed the study.

### Methods for additional analyses (e.g., subgroup analyses) {20b}

Additional analyses will explore potential subgroup differences and interaction effects. Subgroup analyses will stratify by age, gender, baseline stroke severity (NIHSS), and comorbid conditions such as diabetes or hypertension. These analyses will be conducted using stratified chi-square tests for categorical outcomes and stratified Wilcoxon rank-sum tests or mixed-effects models for continuous outcomes. Interaction effects will be assessed with multivariable logistic regression models for binary outcomes. All statistical tests will be two-tailed, with a *p*-value of less than 0.05 considered statistically significant.

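### The stratified tests named for the subgroup analyses do not test whether the treatment effect differs between subgroups; interaction tests are named only for binary outcomes and are not made the basis for subgroup conclusions

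*Protocol article*

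**What the plan says.** Section {20b} of the protocol article gives the aim: "Additional analyses will explore potential subgroup differences and interaction effects". The factors are listed next: "Subgroup analyses will stratify by age, gender, baseline stroke severity (NIHSS), and comorbid conditions such as diabetes or hypertension".

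The methods differ by outcome type:
- Categorical outcomes, and the start of the wording for continuous ones: "These analyses will be conducted using stratified chi-square tests for categorical outcomes and stratified Wilcoxon rank-sum tests".
- Continuous outcomes in full: "stratified Wilcoxon rank-sum tests or mixed-effects models for continuous outcomes".
- Binary outcomes, in the sentence after these: "Interaction effects will be assessed with multivariable logistic regression models for binary outcomes".

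One threshold covers all of them: "All statistical tests will be two-tailed, with a *p*-value of less than 0.05 considered statistically significant".

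Section {20a}, on the main generalized linear model, has its own sentence on interactions: "If the outcomes show statistical significance for the main effects, interaction effects will be used to assess differences between the groups". Section {20b} sets no such condition.

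**The concern.** A subgroup difference is a difference between treatment effects. The stratified tests answer another question under either reading of the word.

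- **Pooled over strata** (Cochran-Mantel-Haenszel for categorical data, van Elteren for ranks): the test asks whether there is an average treatment effect after allowing for the stratum. It tends to be significant when the effect is the same everywhere, and silent when effects cancel.
- **Run separately within each stratum**: each test asks whether there is an effect in that stratum. Finding one stratum significant and the other not is not evidence that the effects differ.

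For binary outcomes the section thus names two procedures that can disagree, both read at 0.05, and does not say which one supports a subgroup statement. For the biochemical indices and inflammatory factors in {12}, no treatment-by-subgroup test is named. At stake is a published subgroup statement for or against benefit that rests on a test of something else.

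**Working it through.** **The plan's own figure.** The protocol gives no figure for the subgroup analyses, so the only one to reproduce is the sample size in {14}. The printed formula with p = (0.136 + 0.333)/2 = 0.2345 and δ = 0.197 gives n = 2 × (1.96 + 0.84)² × 0.2345 × 0.7655 / 0.197² = 72.5 per group. With unpooled variance it is 68.6. The stated 70 lies between them. Then 70/0.90 = 77.8, so 78 per group and 156 in total, as stated.

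**Inputs for the check.** END rates of 33.3% and 13.6% and 78 per group are from {14}. Assumptions: one binary factor splitting each arm evenly (39 per arm per stratum), and the effect patterns in the table.

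**Pooled test, by formula.** With n = 39 per arm, each stratum contributes (n/2)(p_PI − p_AT) = 19.5 × (−0.197) = −3.84 to the numerator. Its variance is ¼ × m(N − m)/(N − 1) with N = 78 and m = 39 × 0.469 = 18.29, which gives 3.55.
- Same effect in both strata: z = −7.68/√7.09 = −2.89. The test is usually significant although no subgroup difference exists.
- Reversed effects: the contributions are −3.84 and +3.84, so the expected z is 0 although the subgroup difference is as large as these rates allow.

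**Interaction test, by formula.** The log odds ratio in a stratum is ln[(0.136 × 0.667)/(0.864 × 0.333)] = −1.154. Its variance is 1/5.304 + 1/33.696 + 1/12.987 + 1/26.013 = 0.334.
- Same effect: the expected difference is 0.
- Reversed effects: the difference is 2.309 in size and its standard error is √0.667 = 0.817, so z = 2.83.

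**Simulation.** 200,000 trials per row, two-sided 0.05, Wald test for the interaction:

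| True pattern | Pooled stratified test rejects | Interaction test rejects | Exactly one stratum significant |
|---|---|---|---|
| Same benefit in both strata | 84.2% | 3.8% | 49.3% |
| Benefit in one stratum only | 27.7% | 31.6% | 54.7% |
| Reversed effects | 4.4% | 82.5% | 49.4% |
| No effect anywhere | 5.0% | 4.4% | 9.8% |

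The pooled column follows the average effect. The last column barely separates identical effects (49.3%) from reversed effects (49.4%), so within-stratum significance carries almost no information on heterogeneity at this sample size. Only the interaction column follows the subgroup difference.

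**The condition in {20a}.** Suppose its condition meant a significant treatment effect and were applied to subgroups. Taking the pooled test as a stand-in for that effect, the reversed pattern would reach an interaction test in only about 4.4% of trials, whatever that test's own power.

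**Coverage by outcome type.** END, severe END and good prognosis by mRS are binary, as is event recurrence if analysed that way; {20b} names an interaction test for these. For the continuous outcomes it names a stratified Wilcoxon test or a mixed-effects model, without saying that a treatment-by-factor term will be fitted.

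**The case against.** The strongest reply is that the remedy largely stands in the same section. The sentence after the stratified tests plans logistic interaction tests for binary outcomes, which include the primary outcome. The contrast of 4% against 82.5% therefore compares two tests that the protocol already contains for END. This stands. A reader might infer that the plan has no way to detect a subgroup difference in END, or would miss a reversal of effect; the document does not support that.

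A mixed-effects model can also carry a treatment-by-factor term. That stands as a possibility, but the text does not state the term and offers the model only as an alternative to the stratified Wilcoxon test.

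A reader might also take the condition in {20a} to govern the subgroup analyses. That sentence belongs to the main model and names no subgroup factor, and {20b} has no such condition. What can be said is that the two sections set different terms for interaction testing and should be reconciled.

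Finally, full reversal is an extreme pattern that nothing in the document suggests, and the analyses are already presented as additional and exploratory. Both points lower the severity. Neither makes the stratified tests suitable for the stated aim.

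**Conclusion.** The point holds in a limited form. The stratified chi-square and stratified Wilcoxon tests do not match the aim of exploring subgroup differences under either reading. A valid test is planned for binary outcomes but is not made the basis for subgroup conclusions. None is named for continuous outcomes. {20a} and {20b} differ on whether interaction testing needs a significant main effect.

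The size, for one evenly split binary factor and the protocol's END rates: the pooled test rejects in 84% of trials with no subgroup difference and 4% with reversed effects, and separate tests disagree in 49% of trials with identical effects. The equal strata and effect patterns are assumptions. The figures are for END; none was computed for the continuous outcomes, where the point rests on what each test asks.

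The interaction test is the right test but not a strong one here: its power is about 32% when benefit is confined to one stratum, so a non-significant interaction would not show that the effect is uniform. The primary END comparison and the sample size are unaffected. Severity is minor.

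**What to change.** In {20b}, drop the stratified tests as the basis for subgroup conclusions. For each listed factor, fit a treatment-by-factor interaction in the model for that outcome: logistic for binary outcomes, mixed or linear for continuous outcomes. Do so whether or not the main effect is significant, and amend the sentence in {20a} to agree.

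Report the interaction estimate and the within-subgroup effects with 95% confidence intervals, label them exploratory, and make no claim from a within-subgroup p-value. The label matters for the interaction tests too: five factors tested at 0.05 give 1 − 0.95⁵ = 22.6% for at least one false positive per outcome, if the tests were independent.

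The cost is wording. Logistic and mixed models are already named, no new data are needed, and the change can be made before analysis, which {21b} says starts only after all participants have finished. For the inflammatory factors, {20a} specifies paired tests of change, which contain no treatment term, so the model carrying the interaction has to be written out.
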